#### HIIT group

Participants will perform training with supervision, involving walking on a flat or inclined treadmill 3 times a week. The HIIT protocol consists of a 10-min warm-up (at 50–60% of the peak HR), 10 × 1-min intervals at 85–95% of the peak HR separated by 1-min periods of active recovery (at 60–70% of the peak HR), and a final 5-min cooldown, which corresponds to the Borg RPE scale of 16–17. An HR monitor (Polar Electro, Kempele, Finland) will be used to obtain the training HR. The speed and incline of the treadmill will be continuously adjusted to ensure that each training session is performed at the prescribed HR.

#### MICT group

Similar to the HIIT group, the participants in the MICT group will perform training with supervision, involving walking on a flat or inclined treadmill 3 times a week. Corresponding to the amount of exercise (exercise intensity × duration) of the HIIT sessions, each MICT session will consist of a 5-min warm-up period and a 5-min cooldown period at 30% of the peak HR, separated by 35 min of exercise at 65–75% of the peak HR. An HR monitor (Polar Electro, Kempele, Finland) will be used to obtain the training HR. The speed and incline of the treadmill will be continuously adjusted to ensure that each training session is performed at the prescribed HR.

### Measurements

The research assistants who blinded to group allocation will collect baseline data from the patients, including age, course of the disease, height, weight, blood pressure, smoking history, socioeconomic status, time since retirement, and history of antidiabetic medication. These assessments will provide a comprehensive overview of the participants’ characteristics. The primary outcome measures of the study will be the HbA1c and BDNF levels. Additionally, the secondary outcome measures will include physical activity levels, anthropometric parameters (weight, waist circumference, hip circumference, and BMI), physical parameters (including fat percentage, muscle percentage, and the fitness rate), cardiorespiratory fitness indicators (blood pressure, the heart rate, vital capacity, and maximum oxygen consumption), biochemical indicators (high-density lipoprotein, low-density lipoprotein, triglyceride, total cholesterol, and HbA1c), inflammation level (C-reactive protein), cognitive function (assessed through reaction time and dual-task gait test performance), and motor function (evaluated through static balance, dynamic balance, single-task gait test performance, and grip strength). To collect these data, participants will be assessed before the start of the intervention and again after the 12-week intervention. Notably, all exercise tests and data collection will be conducted by research assistants blinded to patient group allocation.

### Primary outcomes

#### Glycosylated hemoglobin

To measure HbA1c levels, venous blood samples will be collected in the morning from participants in a fasting state, both before and after the 12-week intervention period. The blood samples will be gently mixed by inverting them multiple times and then allowed to stand at room temperature for 2 h. Afterward, the samples will be centrifuged at 3,000 rpm for 5 min at 4°C. The determination of HbA1c content will be conducted using a fully automated HbA1c analyzer through high-performance liquid chromatography. Each index will be recorded twice to ensure accuracy, and the average value of the two measurements will be used for statistical analysis. In this study, a HbA1c change of 0.2% will be considered the minimum effect size that would have clinical significance and would be of interest in comparisons between the HIIT or MICT groups and the guideline group. HbA1c is an excellent indicator for long-term blood glucose level for 3 months.

### Brain-derived neurotrophic factor

Fasting participants will provide blood samples before and after the 12-week exercise intervention to measure serum BDNF levels. The analysis of serum BDNF levels will be performed using an enzyme-linked immunosorbent assay (ELISA) kit in accordance with the instructions provided by the manufacturer. BDNF is considered an indicator of neuroplasticity and cognitive function, and decreased BDNF levels have been associated with cognitive (Zhen et al., 2013).

### Secondary outcomes

#### Physical activity test

We will employ the Actigraph GT3X (USA), a triaxial accelerometer operating at a frequency of 30 Hz with a 10-s interval, to monitor participants’ physical activity. Prior to the test, we will thoroughly explain the purpose, requirements, and procedures to the participants. The accelerometers will be worn on the right anterior superior iliac spine for a week, except during activities involving water, such as bathing and swimming. Throughout the monitoring period, participants will wear the accelerometers continuously, except during water-related activities, for a minimum of 10 h per day, spanning five working days (Monday to Friday) and two rest day (Saturday and Sunday), ensuring the collection of valid data. To assess physical activity, various parameters will be measured, including average metabolic equivalents (METs) and sedentary time. Data analysis will be conducted using ActiLife 5.0 analysis software.

### Blood pressure (BP) and heart rate

BP will be measured using the Accoson sphygmomanometer (Accoson, Ayrshire, UK), and HR will be measured using the Omron HEM 3 automated blood pressure machine (Omron, Osaka, Japan). Doctors will conduct the tests while participants maintain a seated position.

### Cardiorespiratory fitness

Vital capacity will be tested using an electronic spirometer. Cardiopulmonary exercise testing (CPET) will be performed with a cycle ergometer (Ergoline, Germany), and a ramped test protocol of 15 W/min at 60 ± 5 rpm, continued until volitional exhaustion. A 12-lead electrocardiogram (ECG) device will provide continuous monitoring during the test, and respiratory gas analysis will be assessed in a breath-by-breath manner with a computerized metabolic cart (Schiller CS-200 Ergospirometry, Switzerland). The ventilatory anaerobic threshold (VO_2_AT) will be assessed using the V-slope method by two independent clinicians. In cases where the VO_2_AT deviation is over 10% between the two clinicians, a third clinician will be asked to provide an additional assessment of the VO_2_AT. An average of the two nearest values will be selected. VO_2_peak will be recorded as the average value of VO_2_ during the final 30 s of the test and expressed in ml/kg/min. Cardiopulmonary exercise testing (CPX) will be performed at baseline and at the end of 12 weeks. CPET will be repeated using the same protocol as the baseline test and performed at the same time of day. Cardiorespiratory fitness is an objective measure of physical fitness and has been recognized as protective indictor against cardiovascular events, T2DM and all-cause death.

### Anthropometric parameters

A Seca 213 stadiometer (Seca; Hamburg, Germany) will be used to measure height and weight, and tape will be used to measure the waist and hip circumference. Finally, the BMI (kg/m^2^) of participants will be calculated using the following formula: body weight (kg)/[(body height*body height)m^2^]. BMI is a widely used indictor for obesity and risk factor for cardiovascular events in patients with T2DM.

### Percent body fat

An Inbody 770 (Inbody Co., LTD., Seoul, Republic of Korea) scan will be used to conduct body fat tests. The Inbody 770 device has reliability and validity for body composition assessment (Poblete Aro et al., 2015). Participants will stand barefoot on a platform with electrodes and undergo measurement through hand-held handles. Finally, the body fat percentage of participants will be calculated using the following formula: body fat weight/total weight. There is a significant association between body fat percentage and the risk of cardiovascular events in patients with T2DM.

### Blood glucose, blood lipids and C-reactive protein

During the study, blood samples will be collected from participants before and the 12-week exercise intervention. Blood collection will be performed in the next morning after overnight fast. Four milliliters of venous blood will be drawn, thoroughly mixed by shaking, and allowed to stand at room temperature for 2 h. Subsequently, the blood will be centrifuged at 4°C and 3,000 rpm for 5 min. The resulting supernatant will be stored in a refrigerator at −70°C. To assess various parameters, including glucose, high-density lipoprotein cholesterol (HDL-C), low-density lipoprotein cholesterol (LDL-C), triglyceride (TG), total cholesterol (TC), and C-reactive protein (CRP), a fully automated analyzer (7,071°) will be utilized. Each index will be measured twice, and the average value will be used for statistical analysis. Fasting blood glucose is an indicator for blood control during the night. Similarly, blood lipid levels are strong risk factors for incidence of cardiovascular events, regardless presence of T2DM.

### Reaction time

Before the test, the entire testing process will be explained by researchers. Response times reflect cognitive function, impaired response times is an indicate of impaired daily function in patients with T2DM (Wong et al., 2014). During the test, the participants will press the start button and wait for the signal to be sent. When any signal is presented, the participants should press the button as fast as possible. After the signal disappears, the participants should press the start button again and wait for the next signal to be presented, for a total of 5 signals. After the participants complete the fifth signal response, the signal key will emit a prompt sound, which indicates the end of the test. There will be three tests in total, and the best score will be recorded.

### Single- and dual-task gait tests

Before conducting the test, the researcher will explain the specific requirements of the single- and dual-task gait tests and allow the participants to practice on the Footscan gait system (RsScan International, Olen, Belgium). Our previous study demonstrated the reliability and validity of the Footscan gait system in testing gait function in the elderly population (Yan et al., 2022). Gait can reflect motor and cognitive function in patients with T2DM, and the decline in dual-task gait test performance was significantly associated with motor and cognitive dysfunction in patients with T2DM (Herings et al., 2022). During the formal test, participants will be instructed to walk at their normal pace for a total of five trials. Following a brief break, a dual-task gait test will be conducted, in which participants will be instructed to walk at their normal pace while simultaneously performing addition and subtraction tasks aloud, with numbers ranging up to 100. The results obtained will be based on the average of the five trials conducted. The main parameters measured during the single- and dual-task gait tests will include gait velocity, stride length, stride width, and gait cycle. These parameters provide valuable insights into the participants’ walking abilities and help to identify any potential changes or differences between single- and dual-task walking conditions.

### Grip strength

Grip strength will be measured using a grip strength dynamometer. As a convenient test, grip strength has been shown to reflect muscle quality (Boonpor et al., 2021). Participants will be instructed to assume a standing position with their arms fully extended. They will be asked to maintain a firm grip on a dynamometer, with the size of the grip adjusted to accommodate their palm size. Three measurements will be taken for each hand to ensure accuracy and reliability. To prevent any potential errors, the dynamometer will be cleared before each test. This will ensure that any residual tension or previous measurements do not influence the results. The maximum grip strength achieved during the three measurements for each hand will be recorded as the final maximum grip strength value for that hand.

### Static balance

Static balance function will be assessed by instructing the participant to stand on one foot with their eyes closed. Impaired static balance is a potential risk factor for fall (Dixon et al., 2017). During the test, participants will be instructed to lift one foot, and the tester will start the timer. The test will continue until the supporting foot moves or the raised foot lands on the ground, indicating the end of the trial. Both legs will be tested three times each to determine the maximum value achieved. To ensure accurate results, a 30-s break will be provided between each test. This break serves to minimize the effects of fatigue and other factors that could influence performance.

### Dynamic balance

The Y balance test (YBT) will be used to test the dynamic balance function of the participant. Our previous study demonstrated the reliability and validity of the YBT in testing dynamic balance function in the elderly population (Yan et al., 2022). Decreased dynamic balance function static balance is a potential risk factor for fall (Dixon et al., 2017). Prior to the commencement of the YBT, participants will receive clear instructions and engage in practice sessions to ensure their understanding and proficiency in performing the test. During the test, participants will stand barefoot and begin by placing their dominant leg on a support board, with their hands at their waist. They will aim to maintain their balance while exerting force with the non-supporting leg to push the indicator as far as possible. Subsequently, they will carefully return their body back to the initial test position. The same procedure will be repeated with the non-dominant leg. To obtain accurate and reliable results, each participant will perform three trials with each leg. The average of the three trials for each leg will be used for subsequent analysis. To account for the influence of participants’ height on the test results, the YBT data will be normalized. Normalization will be achieved by calculating the ratio of the extension distance to the leg length distance and multiplying it by 100%. By normalizing the YBT data, we can effectively account for the individual’s height and obtain a standardized measure of their performance. This allows for meaningful comparisons and analysis across different participants.

### Statistical analysis

The intention-to-treat principle will be employed for all analyses, ensuring that participants are analyzed according to their assigned treatment groups. Linear mixed models will be utilized, incorporating participant and baseline values as random effects, to estimate changes within groups (with a difference between groups of *P* < 0.1) for all outcome measures. To address missing data, the multiple-imputation method will be employed to test its influence on the analysis. All statistical analyses will be conducted using R software (version 4.0.2, the R Project for Statistical Computing^2^). The hypothesis tests will be two-sided, and statistical significance will be defined as *p* < 0.05. For the primary outcomes, multiple will be not necessary as the α value have been allocation in the sample calculation. Importantly, no adjustments for multiple comparisons will be made for secondary outcomes, and therefore, their interpretation should be considered exploratory in nature. Subgroup analyses based on sex, duration of T2DM, and BMI will also be performed to examine potential variations within these subgroups. A per-protocol sensitivity analysis will be applied.

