### Sample size calculation

We assumed MICT is superior to guideline-based group in glucose control and cognitive function. Moreover, we also test whether HIIT was superior to MICT group. Limited studies have compared the HIIT or MICT and guideline groups on HbA1c or BDNF. We assumed a glycosylated hemoglobin (HbA1c) mean (SD) difference in change of 0.2 (0.3)% between MICT groups and guideline groups. Based on previous study (Terada et al., 2013), an additional mean (SD) difference in change of HbA1c of 0.2 (0.3)% between HIIT and MICT was assumed. The mean difference (SD) in BDNF levels was assumed to be 1.2 (1.4) ng/ml between MICT and guideline group. Additional 1.2 (1.4) ng/ml for BDNF between HIIT and MICT was assigned (Kovacevic et al., 2020). We will adopt the larger sample size to ensure adequate power. Finally, we intend to enroll 330 participants (110 per group) with a power of 90%, a one-sided α of 0.025 and an expected dropout rate of 20%. The α value of 0.025 will be equal assigned to HbA1c and BDNF. PASS software (version 15.0, NCSS Statistical Software) was used to calculate sample size. If the upper confidence interval of the MD in HbA1c levels between the HIIT or MICT interventions and the reference group falls below zero (<0.0%), HIIT or MICT is considered superior to the reference group in terms of improving glucose control. When the lower confidence interval > 0.0% of the MD in BDNF, it would be declared superior to the reference group for improving cognitive function.

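### The primary α is split between HbA1c and BDNF in the sample-size section, but the analysis section gives two-sided p < 0.05, relies on the split to waive adjustment, and leaves the arm contrasts uncovered

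*Protocol article*

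**What the plan says.** There are two primary outcomes (Protocol article, Measurements): "The primary outcome measures of the study will be the HbA1c and BDNF levels".

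The Sample size calculation section sets the error rate and size: "we intend to enroll 330 participants (110 per group) with a power of 90%, a one-sided α of 0.025 and an expected dropout rate of" (the figure given is 20%). It then divides the α: "The α value of 0.025 will be equal assigned to HbA1c and BDNF". It names two contrasts: "We assumed MICT is superior to guideline-based group in glucose control and cognitive function", and "Moreover, we also test whether HIIT was superior to MICT group". Its superiority rule compares a confidence bound with zero, separately for HbA1c and for BDNF, and gives no confidence level. The HbA1c section brings in HIIT against guideline as a third contrast of interest, speaking of "comparisons between the HIIT or MICT groups and the guideline group". The hypothesis in the abstract also expects both HIIT and MICT to do better than guideline.

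The Statistical analysis section sets the threshold: "The hypothesis tests will be two-sided, and statistical significance will be defined as" p < 0.05. The next sentence reads: "For the primary outcomes, multiple will be not necessary as the α value have been allocation in the sample calculation". Secondary outcomes are left unadjusted and called exploratory.

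**The concern.** Two-sided p < 0.05 spends one-sided 0.025 in the direction of benefit. That is the whole planned α for each outcome, not half of it. The analysis section therefore waives adjustment by pointing to an allocation that its own significance level does not use.

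The allocation is also made over outcomes only. Each outcome carries two or three arm contrasts, each of which can yield its own superiority claim, and the article describes no order or shared control for them.

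At stake is the trial's main verdict. A primary result with a two-sided p between 0.025 and 0.05 counts as superior under the analysis section and not superior under the split.

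**Working it through.** **Inputs.** From the Sample size calculation section: one-sided α 0.025, power 90%, dropout 20%, 110 per arm; HbA1c difference 0.2 with SD 0.3 and BDNF difference 1.2 with SD 1.4, the same for MICT against guideline and for HIIT against MICT. Allocation is 1:1:1. The correlation between the two outcomes is not given; I assume 0 to 0.5.

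**1. Does the sample size show which α was used?** HbA1c has the smaller standardised effect and drives the size. Per arm, n = 2(z_α + z_β)²(SD/δ)², with (0.3/0.2)² = 2.25.
- α = 0.025: 2 × (1.960 + 1.282)² × 2.25 ≈ 47.3, so 48 (49 with the t correction). Divided by 0.8: 60–62.
- α = 0.0125: 2 × (2.241 + 1.282)² × 2.25 ≈ 55.9, so 56 (58 with the t correction). Divided by 0.8: 70–73.

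Neither gives 110. The figure is approached only with additions that the article does not state, such as α = 0.00625 with 90% joint power over four tests (107–114). The sample size does not settle the α.

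**2. The three readings of the text.**
- If 0.025 is halved, each outcome has one-sided 0.0125, which is two-sided 0.025 or a two-sided 97.5% interval. That conflicts with p < 0.05.
- If each outcome gets 0.025, p < 0.05 agrees with it, but nothing was split and the stated reason for no adjustment fails.
- If the primaries are meant to use the halved α despite p < 0.05, that threshold is not written down and the contrasts remain uncovered.

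**3. Chance of at least one false claim of benefit under the global null.** For two independent outcomes and one contrast, 1 − (1 − 0.025)² = 4.9% at one-sided 0.025, and 1 − (1 − 0.0125)² = 2.5% at 0.0125. For several contrasts the arms are shared, so the rates were simulated (2 million draws). Ranges run from outcome correlation 0.5 to 0.

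| Contrasts, over both outcomes | One-sided 0.025 per test (two-sided p < 0.05) | One-sided 0.0125 per test |
|---|---|---|
| One | 4.5–4.9% | 2.3–2.5% |
| MICT–guideline and HIIT–MICT | 9.0–9.7% | 4.6–4.9% |
| All three | 11.6–12.7% | 6.2–6.7% |

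The planned figure is 2.5%. Failing to apply the outcome split doubles the error (4.9/2.5 ≈ 2). The rest of the rise comes from the contrasts.

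**4. Thresholds that hold 2.5% overall (Bonferroni).** Two contrasts: 0.0125/2 = 0.00625 one-sided per test, simulated error 2.4–2.5%. Three contrasts: 0.0125/3 ≈ 0.0042, simulated error 2.2–2.3%.

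**5. Power at those thresholds.** Evaluable per arm: 110 × 0.8 = 88. For HbA1c the standard error is 0.3 × √(2/88) = 0.0452, so δ/SE = 4.42.
- 0.0125: Φ(4.42 − 2.241) = 98.5%
- 0.00625: Φ(4.42 − 2.498) = 97.3%
- 0.0042: Φ(4.42 − 2.638) = 96.3%

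For BDNF, power is at least 99.9% at all three.

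**The case against.** The analysis section does not say outright that the primaries are tested at 0.05. It gives a general threshold, and its next sentence singles out the primary outcomes and refers back to the allocated α. A fair reader may take that sentence as the exception. This stands, and it is why the error rates above are conditional. A reader might infer that the trial's primary error rate simply is several times 2.5%. The text supports only that it would be so if p < 0.05 were used and the contrasts were counted; the unapplied split alone doubles it.

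A reader might also set the chance of a false positive in either direction over all six tests, 21–23%, beside the planned 2.5%. The two are not comparable, since the planned figure is one-sided. The favourable-direction figure for the same six tests is 11.6–12.7%.

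A condensed article may leave the confidence level and the order of contrasts to a fuller document, so their absence alone is no finding, and it would be conjecture to say that a 95% interval will be used. What remains is what the article does state: two levels that do not agree, and a reason for waiving adjustment that fails under each reading.

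Finally, a fixed order starting with MICT against guideline is a real trade-off. If the MICT effect on HbA1c were 0.1 instead of 0.2 (an assumption; SD 0.3, 88 per arm, one-sided 0.0125), then 0.1/0.0452 = 2.21 against 2.241, and that gate would pass only about 49% of the time. No particular order should be imposed.

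**Conclusion.** The concern holds as a contradiction over the primary α, together with a waiver of adjustment that does not do what it claims. It is not shown that the primaries will be tested at 0.05. If they are, false claims of benefit run at about 5% for one contrast over both outcomes, 9–10% over the two contrasts that were sized and 12–13% over all three, against 2.5% planned. If the split is applied and the contrasts are left alone, the rate is still about 5% (two) to 6–7% (three).

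These figures assume the global null, equal arms and an outcome correlation between 0 and 0.5; over that range they change little. The matter needs settling before analysis because it decides which primary results may be called superior.

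**What to change.** In the Statistical analysis section, limit p < 0.05 to the secondary outcomes and replace the sentence on the primaries with a statement that each primary outcome is tested at one-sided 0.0125 overall. Name the contrasts that belong to the primary family, and control them within each outcome by a pre-specified method. Holm or Bonferroni would do (Bonferroni: 0.00625 one-sided per test for two contrasts, 0.0042 for three), as would a fixed order chosen by the sponsor with the trade-off above in view.

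In the Sample size calculation section, put the matching confidence level into the superiority rule: two-sided 97.5% where a test uses 0.0125, or 98.75% (1 − 2 × 0.00625) and about 99.2% (1 − 2 × 0.0042) under the Bonferroni thresholds.

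The cost is wording and a somewhat stricter threshold. HbA1c power per test falls from 99.3% at one-sided 0.025 to 98.5%, 97.3% or 96.3% with 88 evaluable per arm, on the plan's own effect and SD. On those assumptions no extra participants are needed. The article reports recruitment as still under way, so the change can be made and dated before the data are analysed.
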